### Instrumentation

*Maximal tongue strength* is measured by the Iowa Oral Performance Instrument (IOPI) Pro, model 3.1 (IOPI Medical LLC, Woodinville, WA, USA). This is a small, portable instrument connected to an air-filled bulb. Maximal isometric pressure can be measured anteriorly and posteriorly, MIP_a_ and MIP_p_, respectively. The digital display shows the amount of pressure that the tongue produces (in kilopascal, kPa) when squeezing the bulb against the palate. In the anterior position, the proximal end of the bulb is placed immediately behind the upper teeth at the midline of the palate. In the posterior position, the bulb is placed at the level of the transition from the hard to the soft palate. The subjects are instructed to push the bulb as hard as possible against the palate. The highest value of three trials is considered the MIP. Tongue-strengthening exercises are done using the IOPI Trainer, model 3.2 (Fig. 1), which is similar to model 3.1. The device allows the therapist to set a target manually. There is a vertical series of small lights providing visual feedback: the upper light becomes green when the subject reaches the target. The TSE only consists of anterior tongue presses since previous research shows that the increase in tongue strength depends on the localization of the bulb: higher increases of anterior and posterior tongue strength are obtained when training exclusively anteriorly [47]. Patients are instructed to squeeze the bulb against the hard palate until the upper light becomes green and are asked to hold this effort for 3 s [48].

**Fig. 1 Fig1:**
[figure not shown]
Iowa Oral Performance Instrument, model 3.2 (IOPI Medical LLC, Woodinville, WA, USA)

*Maximal chin-tuck strength* (in Newtons, N) is measured by means of a dynamometer (Microfet™, Biometrics, Almere, The Netherlands) (Fig. 2). Patients are asked to place their chin on the chin bar and keep their mouth and teeth closed. A fixed belt stabilizes the patients’ head. They are instructed to press their chin down as hard as possible. The highest value of three trials is considered the maximal isometric chin-tuck strength. Based on this value, the resistance level can be assessed using the conversion table from Kraaijenga et al. (value from 1 to 6) [38, 45]. The CTAR exercises are performed using the Swallowing Exercise Aid (SEA) (Fig. 3). It is a medical device remodeled by a technician of the Netherlands Cancer Institute by adding a chest bar to one of the mouthpieces of the commercially available TheraBite Jaw Mobilization device (Atos Medical, Hörby, Sweden) [38]. The ActiveBand can be placed at various, marked positions depending on the desired resistance. The minimal resistive load is 4 N (position 1) and the maximal resistive load is 50 N (position 6). Subjects are asked to hold the device with one hand, place the chest bar against the chest and put their chin on the chin bar. They are instructed to press the chin bar towards the chest bar and hold this effort for 3 s. At every fifth repetition, patients are asked to press the chin bar against the chest bar and swallow as hard as they can (effortful swallow).

**Fig. 2 Fig2:**
[figure not shown]
Examination frame and dynamometer (MicrofetTM, Biometrics, Almere, The Netherlands)

**Fig. 3 Fig3:**
[figure not shown]
Swallowing Exercise Aid (SEA)

### Outcome measures

The primary outcome measure of this study is the swallowing function, based on scores of the Mann Assessment of Swallowing Ability-Cancer (MASA-C) [49]. Next to this measurement, patients are asked to fill out the Eating Assessment Tool-10 [50] and a Visual Analog Scale. The Functional Oral Intake Scale [51] is filled in by a SLP. The swallowing function is assessed at baseline, weekly during the weeks of exercise, immediately after CRT and 1 and 3 months after CRT (Table 1).

There are three secondary outcome measures: (1) degree of compliance, (2) muscle strength and (3) QOL.

The degree of compliance is expressed as the total number of exercises performed per week, based on daily patient (group 1 and 2) and therapist (group 3) registration. The number of performed tongue-strengthening exercises is recorded automatically by means of the IOPI. In group 2, the degree of compliance is also expressed by the time spent on the app, which is registered automatically. The compliance is assessed during the first 4 weeks of CRT. MIP_a_, MIP_p_ and strength of the suprahyoid muscles are examined at the same time as the swallowing function (Table 1) and are measured using the IOPI and a dynamometer. The Swallowing Quality-of-Life Questionnaire [52] and the Dysphagia Handicap Index [53] examine the swallowing-related QOL and are assessed at baseline, at the end of CRT and 1 and 3 months after CRT (Table 1).

All these evaluations are performed by a SLP.

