### Study design

The study will be a multicenter RCT. All patients will be training five times a week during the first 4 weeks of CRT. Baseline measurements will be done before the start of CRT. Every week during the training, immediately after CRT and at 1 and 3 months following treatment, patients will be evaluated by radiation therapists and SLPs. Table 1 shows an overview of the study visits and evaluations during the study. Prophylactic swallowing exercises are the same in all groups and comprise evidence-based exercises targeting the main muscle groups involved in swallowing; namely, muscles involved in tongue strength, pharyngeal contraction and laryngeal elevation/upper esophageal sphincter opening. These strengthening exercises include tongue-strengthening exercises (TSE) and chin-tuck against resistance (CTAR) combined with an effortful swallow. First, TSE will be performed since tongue strength is the main bolus-driving force and reduced tongue strength can cause oral and pharyngeal residue and aspiration [34–36]. Second, CTAR exercises are used since they have a significant impact on the suprahyoid muscles, with a positive effect on laryngeal elevation and upper esophageal sphincter opening [37, 38]. The third exercise consists of effortful swallows in combination with the chin-tuck. Effortful swallows have been shown to improve the tongue-base posterior motion and can increase tongue-base pharyngeal-wall pressures [39]. It is hypothesized that the chin-tuck in combination with an effortful swallow stimulates the pharyngeal musculature [38].

**Table 1 Tab1:** Study visits and evaluations

			Study period				
	Enrollment	Allocation	Post allocation				
Time point	*Pre RT*	*Between enrollment and start RT*	*Weeks 1–4 of RT*	*Weeks 5–7 of RT*	*End of RT*	*1 month after RT*	*3 months after RT*
Enrollment:							
Eligibility screen	X						
Informed consent	X						
Allocation		X					
Interventions:							
*PSE – control group*			X				
*PSE – app group*			X				
*PSE – therapist group*			X				
Assessments:							
*Patient, disease and therapy characteristics*	X						
*Swallowing function*	X		X		X	X	X
*Muscle strength*	X		X		X	X	X
*Impact of mucositis*	X		X		X	X	X
*Quality of life*	X				X	X	X
*Attitudes towards exercises*			X				
*Overall fatigue*	X		X				

*RT* radiotherapy, *PSE* prophylactic swallowing exercises

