The different exercises described above alternate during the sessions: all subjects start their first session with TSE and perform CTAR exercises and effortful swallowing in the next session. Tongue-strengthening exercises consist of 120 tongue presses and are divided into 12 sets of 10 repetitions with a 30-s rest between sets and with the target level set at 80% of 1 repetition maximum (1RM, i.e., the maximum amount of pressure that can be generated in one repetition) [34, 40–44]. The next session CTAR exercises and effortful swallows are performed. Each CTAR session consists of 150 chin-tucks against resistance at a target level of 60–70% [45] of the 1RM (i.e., in this study, the maximum chin-tuck strength that can be generated). These chin-tucks are divided into 30 sets of five repetitions with an effortful swallow at every fifth repetition. In both tongue and chin-tuck exercises, a successful repetition was defined as reaching the target level and holding the contraction for 3 s, using the green light (TSE) as biofeedback or tactile biofeedback (CTAR). According to the principle of progressive overload, maximal tongue strength and strength of the suprahyoid muscles and correspondent levels of resistance are measured at baseline and recalculated subsequently every week [44].

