All subjects will be randomly assigned into the previously defined groups: control group, app group and therapist group. The groups differ in degree and kind of adherence-improving measures. All groups have some of these measures in common. Restricting the duration to the first 4 weeks of CRT is a first method to increase compliance since the literature shows that in the last 2–3 weeks of therapy the feasibility of completing exercises decreases [20, 33]. Receiving visual and tactile feedback on their performance via the therapeutic devices is a second method. The differences in adherence-improving measures between the groups are illustrated in Table 2. The first group (control group) will perform the exercises at home, without supervision of a SLP but with a counseling session of 10 min every week. Group 2 (app group) practices at home but receives continuous counseling and gets instructions by videos via an application on a tablet, developed in collaboration with Cyborn, Antwerp, Belgium (www.cyborn.be). Generally, mobile health applications are considered to be possible tools to improve traditional health care [46]. By means of gamification, the app helps, supports and motivates the patients to practice. The app registers when the patients practice, how many repetitions they do and when they succeed in doing the exercises. Group 3 (therapist group) is given face-to-face therapy and will be counseled by a SLP five times per week. All patients will complete the first session with supervision of the SLP, irrespective of their group. The intervention will be discontinued on participant request or in case of worsening disease, requiring major changes in treatment. Reasons for discontinuing will be stored in a database.

**Table 2 Tab2:** Study design

Inclusion	*n* = 150		
Stratified randomization	*n* = 50 Control group	*n* = 50 App group	*n* = 50 Therapist group
Therapy schedule	• 5x/week (30–40 min)	• 5x/week (30–40 min)	• 5x/week (30–40 min)
	• 4 weeks	• 4 weeks	• 4 weeks
	• Home practice	• Home practice but app-supported	• Therapist supervised
Exercises	• TSE	• TSE	• TSE
	• CTAR	• CTAR	• CTAR
	• Effortful swallow	• Effortful swallow	• Effortful swallow
Adherence measurements			
• Supervision	No (home practice)	No (home practice – app)	Yes (face-to-face therapy)
• Counseling	Counseling 1x/week by SLP (10′)	Counseling 1x/week by SLP (10′) & continuous counseling via app	Counseling by SLP 5x/week

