#### Data analysis

Patients will be analyzed in the groups to which they are assigned (intention-to-treat). Descriptive statistics will be used to summarize patient characteristics per treatment group. Data will be analyzed using linear mixed-effects models with group, time and group by time interaction as fixed effects. A random intercept will be added to account for correlation between measurements coming from the same individual. When one or more overall effects are significant, post-hoc pairwise testing with Bonferroni-Holm correction for multiple testing will be performed. Missing data is assumed to be missing at random (MAR) and, thus, will be ignored in the analyses. By using mixed-effects models for the analysis, we can incorporate all information on the available time points. If more than 15% of the data is missing, a sensitivity analysis will be conducted by using multiple imputation. Results of the original analysis of the available cases will be interpreted in the context of sensitivity analysis.

Additionally, the impact of adherence, HPV status, dosimetry and mucositis on the different functional endpoints will be studied in exploratory linear mixed-effects models. Fixed main-effects and interactions with group for all these factors will be evaluated.

More details on the primary, secondary and exploratory analyses can be found in the statistical analysis plan.

A *p* value of less than 0.05 will be considered statistically significant. All analyses will be conducted using SPSS Statistics version 25 (IBM, Chicago, IL, USA) and R software (R Foundation, Auckland, New Zealand).

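### Compliance is registered by patients in the two home groups and by therapists in the third, so comparisons with the therapist group mix delivery with recorder

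*Protocol article*

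**What the plan says.** All references are to the protocol article.

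- **Outcome measures** lists degree of compliance as the first of three secondary outcomes. It is a weekly total of exercises done, "based on daily patient (group 1 and 2) and therapist (group 3) registration".
- The next sentence adds a device record: "The number of performed tongue-strengthening exercises is recorded automatically by means of the IOPI". It names no group. Table 2 gives all three groups instrumental feedback, which fits use of the device throughout.
- The app group has extra records: "In group 2, the degree of compliance is also expressed by the time spent on the app, which is registered automatically", and in Study design "The app registers when the patients practice, how many repetitions they do and when they succeed in doing the exercises".
- No automatic count of chin-tucks or effortful swallows is described for the control or therapist group.
- The article does not say which source prevails for tongue exercises when registration and device disagree.
- **Minimization** states that the trial is open-label and that outcome assessment is not blinded.
- **Data analysis** compares groups with linear mixed models. It also uses adherence as an explanatory factor, with group interactions, in exploratory models of the functional endpoints.

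**The concern.** A between-group comparison needs the outcome measured the same way in every group. Here the person who counts is fixed by the allocation. Home patients judge and write down their own repetitions, while in the third group a professional who is present does so. Study design calls a repetition successful only if the target level is reached and held for 3 seconds. If recorders apply that standard, a supervising therapist can check it more readily than a patient alone.

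Randomization, a larger sample or the mixed model cannot remove such a difference, because it coincides exactly with group membership. The effect on compliance is part of the first stated aim of the trial. A recorder difference could hide a real benefit of therapist support or create an apparent one, and it would carry over into the exploratory models that use adherence.

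**Working it through.** **Figure to reproduce.** The plan states no effect size, standard deviation or sample size for compliance. Its sample size (111, raised to 150 for dropout) is for the MASA-C score and does not bear on this point.

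**Inputs from Study design.**

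- Frequency: "All patients will be training five times a week during the first 4 weeks of CRT", so 5 × 4 = 20 sessions. Sessions alternate, starting with tongue exercises; strict alternation gives 10 of each type.
- Tongue sessions: "Tongue-strengthening exercises consist of 120 tongue presses".
- Chin-tuck sessions: 150 chin-tucks, with the effortful swallows falling on every fifth repetition and so included in the 150.

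**Step 1: how much the device covers.**

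- Tongue presses: 10 × 120 = 1,200.
- Chin-tucks: 10 × 150 = 1,500.
- Total: 2,700. Tongue share 1,200/2,700 = 44.4%; chin-tuck share 55.6%.

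The prescribed tongue count also varies by week. Weeks 1 and 3 have three tongue sessions (360 presses) and weeks 2 and 4 have two (240). A raw weekly count would move with the schedule, so a share of presses prescribed is the better scale.

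**Step 2: what over-reporting does to each contrast.** Let *b* be average over-reporting by home patients, in percentage points of prescribed repetitions.

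- Therapist minus a home group: observed difference = true difference − *b*.
- The same contrast if the device supplies the tongue component: true difference − 0.556*b*.
- The same contrast on device-recorded tongue presses only: no recorder term.
- App minus control: both use patient registration, so *b* cancels if it is the same on average in both groups.

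The documents give no value for *b*, so 5, 10 and 20 points are assumed.

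**Step 3: effect on a test.** Assume equal true adherence, a standard deviation of 30 points (not in the documents), the planned 50 per group and a plain two-sided 0.05 comparison of the therapist group with one home group. The standard error is 30 × √(2/50) = 6.0. For a bias of *d* points, the probability of a false significant difference is Φ(*d*/6 − 1.96) + Φ(−*d*/6 − 1.96).

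| Assumed over-reporting | Bias, all repetitions registered | False significance | Bias, tongue count from device | False significance |
|---|---|---|---|---|
| 5 points | 5 | 0.13 | 2.8 | 0.08 |
| 10 points | 10 | 0.39 | 5.6 | 0.15 |
| 20 points | 20 | 0.92 | 11.1 | 0.46 |

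With no recorder difference the probability is 0.05. The plan's pairwise tests follow an overall test and are Holm-corrected, so the actual probabilities would differ. The table shows only how quickly the error grows.

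**The case against.** **The device count is already in the plan.** The sentence on automatic recording stands directly after the registration clause, in the paragraph that defines compliance. It can fairly be read as supplying the tongue component in every group. This stands: compliance is not purely self-reported at home, and on this reading the bias falls to about 56% of its size. It does not settle the matter, because the article does not say which source prevails and the remaining repetitions still have different recorders.

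**The scope is limited.** This also stands. The app-versus-control contrast shares a recorder, compliance is secondary, and over-reporting is plausible but undocumented. If patients instead forget to write down exercises they did, the bias reverses and the therapist-group advantage is overstated.

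**A stronger reading concerns missing diaries.** Data analysis says "Missing data is assumed to be missing at random (MAR) and, thus, will be ignored in the analyses". A reader might infer that patients who stop exercising leave blanks, that the blanks are dropped, and that home-group adherence is inflated a second time. The article does not support this. Suppose, as an assumption, that half of days are exercised and the diary is completed on 90% of exercised and 50% of other days. Dividing by completed days gives 0.45/(0.45 + 0.25) = 64% against a true 50%. But the outcome is a weekly total, not a share of completed days. Summing recorded days gives 0.5 × 0.9 = 45%, which is too low. The missing-data sentence is general, and the article does not state how blank days are coded. That may be in the statistical analysis plan, to which the article refers. Multiple imputation above 15% missing is also planned, although it usually rests on the same assumption.

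**Conclusion.** The point holds for the recorder and for the contrasts of the therapist group with either home group. Under over-reporting, the therapist-group advantage is understated by the full amount if all repetitions are taken from registration, or by about 56% of it if the device supplies the tongue count. For the assumed 5, 10 and 20 points, that is 5, 10 and 20 or 2.8, 5.6 and 11.1 points. These sizes and the direction are assumptions. What the documents establish is that the recorder differs by group.

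No conclusion is drawn about the handling of missing diaries. A reader might also infer that the trial's main result is at risk. It is not: the MASA-C analysis does not use these counts. This is a secondary-outcome issue to settle before the compliance data are analysed, not a condition for the primary analysis.

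**What to change.** 1. Make the automatically recorded tongue-press count, divided by the presses prescribed for that week, the main between-group compliance comparison in all three groups. First confirm that the record is kept for every group, since the sentence does not name them.
2. Keep the registered weekly total, including chin-tucks and effortful swallows, as a supportive outcome, and state the recorder difference as a limitation.
3. In the control and app groups, compare registered with device-recorded tongue counts to estimate over- or under-reporting.

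A rule that counts every blank diary day as zero is not advised. Under the day-level assumptions above it gives the same 45% against a true 50%, and it would penalise the home groups for chin-tucks that no device can confirm.

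The cost is a wording change and an export of counts the trial already records. The downside is that the main comparison covers only tongue exercises, about 44% of prescribed repetitions. Chin-tuck compliance can still be compared across groups only through different recorders.

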### Confounders

#### Patient, disease and therapy characteristics

Patient and situational characteristics are questioned at baseline and include age, gender, educational level, social status, experience with mobile phones, tablets, etc. and the presence of support from family or friends. The question about the experience with mobile phones and tablets is an open question that allows the patients to answer extensively. The question about the support is a closed question: yes/no and who. The NEO Five Factor Inventory is used to examine the personality of the patient [54]. The disease and therapy characteristics include location of the carcinoma, stage, treatment, fractionation, TNM classification (TNM7) and human papillomavirus (HPV) status. This information is gained by radiation oncologists, head and neck surgeons and otolaryngologists.

#### Evaluation of the impact of mucositis

The Oral Mucositis Weekly Questionnaire [55] is used to measure the symptoms of mucositis and the impact on the patient’s well-being and function.

#### Evaluation of attitudes towards exercising, motivation and fatigue

The attitudes on exercises are surveyed by the questionnaire of Sluijs, Kok and Van der Zee [56] and the overall fatigue of the patients is evaluated by the Multidimensional Fatigue Inventory [57] (Table 1).

### Data management and monitoring

The datasets generated during the study will be stored in a non-publicly available repository. All clinical record forms are collected and managed using REDCap (Research Electronic Data Capture) electronic data capture tools hosted at Ghent University Hospital [58]. This is a secure, web-based application designed to support data capture for research studies. All patient information (except identifying information), questionnaires and measurements are stored for 20 years. The researchers from each participating institution have access to the data of their patients. All data is pseudonymized and patients’ details are encoded. The principle investigator and the researcher at the University Hospital in Ghent manage the entire database.

In order to avoid introducing bias, no interim analyses will be performed. As the experimental interventions caries minimal risks, no data monitoring committee will be implemented, nor will there be a stopping procedure.

There is no anticipated harm and so no compensation for trial participation. After completing the trial, participants will be followed by the radiation oncologist and head and neck surgeon or otolaryngologist and, if necessary, they will be referred to any other specialist.

Serious adverse events will be reported to the Ethical Committee of the central study center by means of a yearly line-listing system.

